##### Blood sample collection and storage

3.3.2.8

Non fasting blood samples for HbA1c, plasma glucose (in Flouride-EDTA tube), serum lipids and adiponectin will be collected from hospital phlebotomy services or by qualified Research Nurses at each site. Following collection, samples will be processed within 30 min and stored at −80 °C until analysis.

#### Phase 3: evaluation of the cost effectiveness, cost utility and workload impacts of the intervention

3.3.3

The primary outcome for economic evaluation is the Quality Adjusted Life Years (QALYs), as measured by EQ5D-5L that will be completed at baseline and at the follow-up assessment for both groups (primary RCT and nested observational RCT).

The Australian health sector and societal perspectives will be used for the analyses to reflect the different decision makers and contexts and per the current guidelines for reference cases in economic evaluations. The health sector costs include those paid by the government of primary and acute care, medication costs, and ambulatory costs as well as the out-of-pocket costs of health care resources paid by the participants during the trial period. Societal costs comprise the health sector costs in addition to the costs of patient transportation (costs per km travelled for visits to health care providers), food and effects on productivity (labour market earning loss of paid work and unpaid lost productivity due to illness). In addition, costs to carers and/or support person(s) will be determined including direct and indirect costs.

The intervention costs of using the adapted Perx app will include training and maintenance costs specific for the RCTs. Costs associated with utilisation of psychologists will be included in the health economic analysis of the primary RCT, and may be included in the exploratory subgroup analyses of the nested observational RCT if a difference is found.

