##### Screening and allocation of participants to study groups

3.3.2.4

Participants will be screened using two validated screening questionnaires: the Kessler Psychological Distress Scale (K10) [21] and the Problem Areas in Diabetes (PAID) scale [22]. The K10 is a validated and widely used self-reported psychological screening tool consisting of 10 questions about emotional states, each with a five-point Likert response scale ranging from 1 (none of the time) to 5 (all of the time). K10 total scores range from 10 to 50 with higher scores indicating greater levels of psychological distress [21]. Participants returning a K10 score ≥20 will be classified as having an MHC. The PAID questionnaire measures diabetes-related emotional distress and is widely used in clinical and research settings [22]. The PAID questionnaire includes 20 items covering emotional challenges experienced by people with diabetes, including worries about managing the condition, fears of potential complications, and feelings of frustration or burnout. Participants returning PAID scores ≥40 will be classified as having an MHC [22]. Participants who self-report a previously diagnosed mental health history or are currently receiving care for a mental health condition from a psychologist will also be classified as having an MHC. Participants identified as having major distress (K10 ≥ 40, PAID ≥20) will be considered for referral to the site psychologist (if available) or their general practitioner for management independent of their allocated group but will not be excluded from the study. (Fig. 1). Results from the screening questionnaires will be used to allocate participants into two studies: those with a mental health condition (MHC; Primary RCT) and those without a mental health condition (No-MHC; Nested exploratory RCT).

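### In the No-MHC trial, inclusion of psychologist costs depends on an undefined observed difference; in the primary RCT the same costs always count

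*Protocol article*

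**What the plan says.** Section 3.3.3 (Phase 3) sets one costing frame: "The Australian health sector and societal perspectives will be used for the analyses". On scope it says "The health sector costs include those paid by the government of primary and acute care, medication costs, and ambulatory costs", and it adds participants' out-of-pocket health care costs. The societal view adds transport, food, productivity and carer costs. No exception is stated for the No-MHC trial. QALYs come from the EQ5D-5L, "completed at baseline and at the follow-up assessment for both groups (primary RCT and nested observational RCT"; the second of these is the trial called nested exploratory elsewhere in the article.

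Two rules for psychologist costs then follow in a single sentence. For the primary RCT: "Costs associated with utilisation of psychologists will be included in the health economic analysis of the primary RCT". For the No-MHC trial they "may be included in the exploratory subgroup analyses of the nested observational RCT if a difference is found".

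Section 3.3.2.4 bears on whether No-MHC participants would use a psychologist at all. It states "Participants returning PAID scores ≥40 will be classified as having an MHC" and, on referral, "Participants identified as having major distress (K10 ≥ 40, PAID ≥20) will be considered for referral to the site psychologist". Section 3.4.3 says that the No-MHC trial could not be powered.

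**The concern.** The perspective of an economic evaluation decides which costs belong in it. The observed result should not. Here the same cost is in scope by rule in one trial and by outcome in the other, under the same perspectives. The condition is also open: the text does not say whether the difference concerns psychologist use, its cost, a clinical outcome or something else, and it names no test or threshold. The word may leaves further discretion once data are in hand.

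In a trial without adequate power, failure to find a difference is weak evidence that there is none. A real cost difference could therefore be left out often, and when it is counted it would tend to be an overestimate. At stake are the No-MHC incremental cost and cost per QALY, and whether they can be set beside those of the primary RCT.

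**Working it through.** **No figure to reproduce.** The article gives no psychologist unit cost, no expected use and no size for the No-MHC trial. The check is a comparison of the text, followed by an illustration on an assumed trigger.

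**Step 1: the two rules side by side (Section 3.3.3).**
- Perspectives: the same for both trials.
- Primary RCT: psychologist costs included without condition, so the plan itself treats them as within these perspectives.
- No-MHC RCT: inclusion permitted if an unspecified difference is found.
- No other section fixes the rule in advance. Section 3.4 says that methods are the same in both RCTs, but this stands in the statistical section and does not settle the costing rule.

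**Step 2: can the cost be non-zero in the No-MHC trial?** A K10 score of 20 or more, or a PAID score of 40 or more, places a participant in the MHC trial. The referral wording lists K10 ≥ 40 and PAID ≥ 20.
- If PAID ≥ 20 alone suffices, No-MHC participants with PAID 20 to 39 can be considered for referral.
- If both scores are needed, K10 ≥ 40 already means MHC, and this route is closed to No-MHC participants at screening.
- On either reading, nothing excludes psychologist use during follow-up.

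**Step 3: illustration.** Assumption, not in the article: the trigger is a two-sided 5% test on the psychologist-cost difference itself, and the component counts as zero when the test is not significant. Let Z be the observed difference in standard errors (SE), Z ~ N(θ, 1), with c = 1.96. For θ = 1:
- P(included) = [1 − Φ(0.96)] + Φ(−2.96) = 0.1685 + 0.0015 = 0.170.
- Mean difference used = θ × P(included) + φ(0.96) − φ(2.96) = 0.170 + 0.2516 − 0.0050 = 0.417 SE. This is 58% below the true 1 SE.
- Mean when included = 0.417 / 0.170 = 2.45 SE, about 2.5 times the true value.

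Simulation with 2 million draws per row gives:

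| True difference (SE) | Included | Mean used (SE) | Bias | Mean when included (SE) |
|---|---|---|---|---|
| 0 | 5.0% | 0.00 | none | 0.00 |
| 0.5 | 7.9% | 0.158 | −68% | 1.99 |
| 1 | 17.0% | 0.417 | −58% | 2.45 |
| 1.5 | 32.3% | 0.843 | −44% | 2.61 |
| 2 | 51.6% | 1.432 | −28% | 2.77 |
| 2.8 | 80.0% | 2.519 | −10% | 3.15 |
| 4 | 97.9% | 3.967 | −1% | 4.05 |

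The variance of the quantity used also moves away from 1: it is 0.28 at θ = 0 and 2.11 at θ = 2. An interval computed as if the cost set had been fixed would not reflect this. Unconditional inclusion has no selection bias in any row. The percentages refer to the psychologist component, not to total incremental cost.

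**Step 4: what carries over.** For any symmetric threshold on the observed psychologist-cost difference, the direction is the same: a real difference is understated on average and overstated when included. If the trigger is another outcome, the bias depends on how that outcome correlates with psychologist cost.

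**The case against.** The best case on the other side is that the sentence carries less than it seems to. It is permissive, it speaks of exploratory subgroup analyses, and it follows directly on the app's own costs, so it may concern a separate utilisation component. The general definition of health-sector costs could already bring psychologist care into the No-MHC totals. A reader might infer that these costs are otherwise set to zero in the No-MHC evaluation; the article does not say so. This stands as a limit on the claim, but it does not rescue the wording. If the totals already include these costs, the conditional sentence contradicts them or adds nothing. If they do not, inclusion turns on the result.

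Further, the true difference may be close to zero. People who are under a psychologist's care, or who report a diagnosed mental health history, go to the MHC trial, so the No-MHC trial should start with little psychologist use. At exactly zero the rule does not bias the mean. This also stands, and it is why the rule can bias the estimate rather than must.

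It is tempting to say that the referral rule sends No-MHC participants to psychologists. The text supports this only if PAID ≥ 20 alone suffices, and even then referral is only considered, with the site psychologist an option only where there is one.

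**Conclusion.** The point holds in limited form. The article states an undefined, results-dependent rule for one cost component in the No-MHC trial, at odds with the perspectives set in the same section and with the unconditional rule for the primary RCT. This is more than a detail left to a fuller plan, because the condition itself is written down.

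The rule can bias the No-MHC incremental cost whenever the true psychologist-cost difference is not zero, and it undermines comparison with the primary RCT. The 17% inclusion and the roughly 2.5-fold exaggeration rest on an assumed 5% test on that cost difference and an assumed true difference of 1 SE. They should not be read as a forecast for this trial. Nothing in the article allows a figure in dollars or in cost per QALY.

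The consequence is small: the primary RCT's economic analysis and the K10 analysis are unaffected, and the No-MHC trial is declared exploratory.

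**What to change.** Replace the conditional half of the sentence in Section 3.3.3 with a fixed rule, for example: Psychologist utilisation costs, taken from the same data sources in both trials, are included in the health-sector and societal cost totals of the primary and No-MHC RCTs regardless of any observed between-arm difference; totals excluding them may be shown as a sensitivity analysis.

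The cost is one sentence and a little more costing work in the No-MHC trial. Table 3 lists hospital service utilisation for both RCTs, and Section 3.3.2.7 invites all participants to consent to data linkage, including mental health ambulatory records for the NSW sites and the same data for the Victorian site. Capture of psychologist visits outside hospital is not stated, but the unconditional rule in the primary RCT needs that source in any case.

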#### Phase 4: scale up plan for intervention

3.3.4

A distribution plan will be developed through health services, diabetes consumer organisations, mental health consumer organisations, and health professional organisations (e.g. Australian Diabetes Educators Association which would then reach those in the private as well as the public sector, Pharmaceutical Society of Australia (PSA) and Pharmaceutical Guild of Australia (PGA) i.e. through pharmacists).

### Statistical analysis

3.4

For the primary outcome variable (K10), a linear mixed effects regression model will be used to show any change, with participant identification number and study site as random effects. Age, gender, ethnicity, socio-economic status, type of diabetes, time and intervention group will be included as fixed effects. A significant interaction between intervention group and time (Baseline vs Follow Up) would indicate that the average change in K10 was significantly different between intervention and control groups [31]. This is the main test of the study and will be subjected to a significance level of α = 0.05. Level of significance will also be indicated using p-values. The effect sizes will be presented as the difference between the average decrease in K10 between intervention groups.

A linear mixed effects regression model will also be used for the secondary outcome variables including a change in; (1) HbA1c (2) PAID and (3) weight in kilograms. To account for multiple testing, a false discovery rate method such as the Benjamini-Hochberg procedure [32], will be adopted for the secondary outcome variables. The effect sizes will be presented as the difference between the average change in outcome between intervention groups. Results will be visualised using a forest plots. For all linear mixed effects models, model diagnostics will be conducted, including, but not limited to (a) examining the residuals for departures from normality, (b) collinearity between covariates using the variation inflation factor and (c) examination of outliers to see if they have too much influence on the results of the analysis. Consequential departures from normality and/or highly influential outliers will be handled using bootstrapping or through transformation of the outcome variable.

A generalised linear mixed effects regression model with a Poisson error model [33] will also be used for the secondary outcome variables; (4) the total number of hospital and/or emergency department admissions and (5) the total number of hospital and/or emergency department admissions due to diabetic keto-acidosis/hyperglycaemia. The models will be examined for over or under dispersion and a more appropriate error model will be adopted if necessary.

Analyses will be adjusted for the following confounders: age, gender, ethnicity, socio-economic status (measured using postcode and Socio-Economic Indexes for Areas tool (SEIFA: Australian Bureau of Statistics), study site, and type of diabetes. The methods adopted will be the same for the primary (MHC) and nested exploratory (No-MHC) RCTs. If necessary, multiple imputation by chained equations [34] will be used to provide intention-to-treat results.

Interviews with participants and healthcare professionals will be conducted utilising the Reach, Effectiveness, Adoption, Implementation, and Maintenance (RE-AIM) framework to evaluate community and clinical impact [35]. The interviews will assess project engagement and implementation, effects of the app, and feedback and recommendations on app content and design. Interviews will be transcribed, coded to identify themes and sub-themes in NVivo and undergo reflexive thematic analysis to present key findings. Reflexive thematic analysis was chosen due to its high recommendation by leading qualitative researchers in the context of healthcare interventions with psychological impact and social outcomes [36]. Briefly, a 6-step process to analysis will involve: 1) data cleaning and familiarisation; 2) coding, where codes relate to features of the data that has been generated; 3) theme development through organisation of codes into broader themes across the dataset; 4) theme review and refinement; 5) theme naming and defining; and 6) reporting of findings.

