### Primary and secondary outcomes

3.1

The primary outcome, psychological distress, will be measured using the Kessler Psychological Distress Scale (K10). Table 1 provides a summary of the primary and secondary outcomes. A parallel health economic evaluation will also be performed.

**Table 1 tbl1:** Primary and secondary outcomes, along with their measurement timepoints, for both the intervention and control groups in the Apps and Peer Support for a Healthy Future and Living well with Diabetes (APHLID-M) study.

Outcome Type	Outcome Variable	Measurement/collection timepoint
Primary	Psychological distress assessed using the K10 questionnaire [21]	Baseline and 6 months post baseline
Secondary	HbA1c determined by an accredited laboratory or point of care testing on blood samples collected from participants	
Secondary	Diabetes-related distress measured using the PAID questionnaire [22]	
Secondary	Weight in kg will be measured using digital scale	
Secondary∗	Total number of hospital and/or emergency department admissions	Baseline (during the six month period prior to commencing the trial) and over the six month duration of the trial
Secondary∗	Total number of hospital and/or emergency department admissions due to diabetic ketoacidosis/hyperglycaemia	
Secondary∗	Total number of hospital and/or emergency department admissions due to hypoglycaemia	

K10; Kessler Psychological Distress Scale, PAID; Problem Areas in Diabetes, ∗ assessed using electronic medical records.

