#### Power calculations

3.4.3

Based on data published previously (behavioural intervention K10 change 21.2 ± 9.4 vs baseline 25.7 ± 9.7 Cohen d = 0.5), a sample size of 64 per group in the primary RCT will be required to identify a moderate effect size of 0.5 between intervention and control group, in a *t*-test model with power = 0.8, alpha 0.05. An additional 14 participants will be included to allow for an attrition rate of 10 % (total n = 142). The nested exploratory RCT (No MHC) is considered an exploratory study as it could not be powered.

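### The main test is in effect a comparison of mean change in K10: it does not condition on baseline, and the stated covariate and site adjustment barely reaches it

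*Protocol article*

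**What the plan says.** Table 1 of the protocol article gives two K10 measurements: "Baseline and 6 months post baseline". Section 3.4 (Statistical analysis) specifies a linear mixed model "with participant identification number and study site as random effects", and "Age, gender, ethnicity, socio-economic status, type of diabetes, time and intervention group will be included as fixed effects". The decision rule is "A significant interaction between intervention group and time (Baseline vs Follow Up) would indicate that the average change in K10 was significantly different" between the arms, and "This is the main test of the study and will be subjected to a significance level of α = 0.05". The reported effect follows the same logic: "The effect sizes will be presented as the difference between the average decrease in K10 between intervention groups".

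Later in the same section the article says "Analyses will be adjusted for the following confounders: age, gender, ethnicity, socio-economic status", and the list goes on to study site and type of diabetes. Baseline K10 is in neither list. No covariate-by-time term is mentioned. Intervention group is a main effect, so the two arms may have different baseline means. HbA1c, PAID and weight are also to be analysed with a linear mixed model, and the same methods apply in the No-MHC trial.

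Section 3.4.3 (Power calculations) states that "a sample size of 64 per group in the primary RCT will be required to identify a moderate effect size of 0.5", with power 0.8 and alpha 0.05 in a t-test.

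**The concern.** With only two timepoints, a group-by-time interaction looks at nothing but each participant's change. Anything constant within a participant (age, gender, ethnicity, socio-economic status, diabetes type, site) cancels. A reader of the article would believe that the main test is covariate- and site-adjusted, when in practice it is not. Site is also the stratifier for the minimisation (section 3.3.2.5).

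The model also ignores the fact that baseline K10 is measured before randomisation, so both arms share one expected baseline mean. Using that fact makes the estimate more precise at no cost in validity. Not using it leaves the result exposed to a chance difference in baseline K10. Section 7 (Discussion) already worries that extra loss to follow-up could prevent detection of an effect of 0.5, so precision matters here.

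**Working it through.** **1. The plan's own sample size.** Two-sample t-test, two-sided alpha 0.05, d = 0.5: 64 per group gives power 80.1%. The figure reproduces. The quoted K10 values give (25.7 − 21.2)/√[(9.7² + 9.4²)/2] = 4.5/9.55 = 0.47, which the article rounds to 0.5.

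**2. Why the interaction is a change-score comparison.** For participant i at time t (0 or 1), the model is

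Y(it) = a + b·group + c·t + d·group·t + covariates(i) + site(i) + participant(i) + error(it).

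Subtracting baseline from follow-up gives

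Y(i1) − Y(i0) = c + d·group + (error(i1) − error(i0)).

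Covariates, site and participant terms are gone, and d is the difference in mean change.

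**3. Numerical check** (simulated data, 142 participants, 8 sites, SD about 9.5, assumed within-person correlation 0.5):

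| Analysis, one complete data set | Estimate | SE |
|---|---|---|
| Raw change score | −8.32502 | 1.51893 |
| Mixed model, no covariates | −8.32502 | 1.51893 |
| Mixed model with covariates | −8.32502 | 1.51893 |
| ANCOVA with covariates | −6.77 | 1.37 |

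Participant and site were random effects in both mixed models. Over 60 further complete data sets (site entered as a fixed effect), estimates with and without covariates agreed to about 1e-13, and the SE ratio was 1.0000. With 10% of follow-up values missing, covariates moved the estimate by 0.08 K10 points on average (maximum 0.22) and the SE by less than 1%.

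**4. Precision lost.** The correlation ρ between baseline and 6-month K10 is not in the article, so it is an assumption, shown over a range. Inputs from section 3.4.3: SDs 9.7 and 9.4, difference 4.5, 64 per arm.

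- SD of change = √(9.7² + 9.4² − 2ρ·9.7·9.4)
- Residual SD after baseline adjustment = 9.4·√(1 − ρ²)
- SE of the arm difference = SD·√(2/64)

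| Assumed ρ | SD (SE), change | SD (SE), adjusted | Power, change | Power, adjusted |
|---|---|---|---|---|
| 0.3 | 11.30 (2.00) | 8.97 (1.59) | 61% | 80% |
| 0.5 | 9.55 (1.69) | 8.14 (1.44) | 75% | 87% |
| 0.7 | 7.40 (1.31) | 6.71 (1.19) | 93% | 96% |

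With exactly equal SDs the variance ratio, adjusted to change, is (1 − ρ²)/[2(1 − ρ)] = (1 + ρ)/2: 0.65, 0.75 and 0.85.

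**5. Against the planned d = 0.5** (equal SDs, 64 per arm): change-score power is 66.0%, 80.1% and 95.2% at ρ = 0.3, 0.5 and 0.7. Baseline-adjusted power is 83.7%, 90.0% and 97.6%. The t-test calculation therefore matches the planned test only at ρ = 0.5, where the SD of change equals the SD of a single K10 score.

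**6. Baseline imbalance.** The change score subtracts the whole baseline difference. ANCOVA subtracts only the slope ρ·9.4/9.7 times it, which is 0.485 at ρ = 0.5. A one-SE chance imbalance, 9.7·√(2/64) = 1.71 points, shifts the change-score estimate by (1 − 0.485)·1.71 = 0.88 points, about a fifth of 4.5.

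**The case against.** The strongest reply is that nothing here is wrong. The outcome is defined as change, the effect is reported as difference in change, the test matches both, and randomisation makes it unbiased with correct type I error. All of that stands, and it keeps this a question of efficiency and accurate description. It does not answer the lost precision or the adjustment that does not operate.

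Second, the article lists variables, not model terms (its list does not even include the interaction it tests), so covariate-by-time terms could be in a fuller document. That is possible. But the article does fix the test, the effect measure and the absence of baseline K10 from both lists, so the baseline part of the point does not rest on what is unstated.

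Third, the identity is exact only with complete pairs, and the article expects 10% attrition and allows for multiple imputation. This is correct, and it is why the claim is that the adjustment has essentially no influence, not none at all.

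Fourth, the power losses rest on a correlation the article does not give. This is also correct. At d = 0.5 and ρ of about 0.5 or more, the planned test meets its 80% target, so a reader who infers that the trial is underpowered goes beyond the document.

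A reader might also infer that recruiting on K10 of 20 or more weakens the correlation and so makes change scores do especially badly. The arithmetic says the opposite. Assume K10 mean 22, SD 9 and ρ 0.6 before selection, and cut at 20. The correlation falls to about 0.44, but baseline variance falls from 81 to 33.6, while slope (0.6) and residual variance (81 × 0.64 = 51.84) are unchanged. The variance of change goes from 0.4²·81 + 51.84 = 64.8 to 0.4²·33.6 + 51.84 = 57.2, so the variance ratio rises from 0.80 to 0.91. Selection narrows the gain from baseline adjustment but does not remove it. It is also only partial, because PAID score, self-reported history or current psychologist care also qualify a participant (section 3.3.2.4).

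**Conclusion.** The point holds as a matter of efficiency and of accurate description, not of validity. As specified, the main test is a comparison of mean change, exact with complete pairs and nearly so at 10% attrition. The stated covariate and site adjustment does essentially nothing to it.

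The cost ranges from about 19 percentage points of power at ρ = 0.3 to about 3 at ρ = 0.7, for a 4.5-point difference. These figures assume 64 evaluable participants per arm, SDs close to those quoted and an assumed ρ. If entry through the K10 threshold dominates, the gain from adjustment shrinks towards the 0.91 variance ratio of the illustration. It would also be small for any secondary outcome with a very high baseline-to-follow-up correlation, possibly weight. The documents do not support calling the planned test biased or the trial underpowered.

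**What to change.** Rewrite the primary analysis in section 3.4 in one of two forms, and name which is primary:

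- **ANCOVA-type model**: 6-month K10 on group, baseline K10, age, gender, ethnicity, socio-economic status and diabetes type, with site as a random or fixed effect.
- **Mixed model with a common baseline mean**: both K10 values as outcomes, time and group-by-time but no group main effect, with the covariates also acting on the follow-up value (covariate-by-time terms).

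The two give near-identical answers with complete data. They differ when follow-up is missing: the mixed model keeps participants who have a baseline value only, while ANCOVA drops them unless they are imputed. In the mixed form, interacting eight sites and every categorical covariate with time uses degrees of freedom that about 128 evaluable participants can ill spare, so the terms should be chosen sparingly.

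Report the adjusted 6-month difference with its 95% CI as the primary effect. Under randomisation it targets the same quantity as the difference in mean change. Use the same form for HbA1c, PAID and weight, and in the No-MHC trial. State in the power section that the t-test calculation does not use baseline.

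The cost is wording only: every variable is already collected, and the sample size need not change. The change should be dated before the study statistician is unblinded.
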